# Target-D: a stratified individually randomized controlled trial of the *diamond* clinical prediction tool to triage and target treatment for depressive symptoms in general practice: study protocol for a randomized controlled trial

**DOI:** 10.1186/s13063-017-2089-y

**Published:** 2017-07-20

**Keywords:** Depression, Clinical prediction tool, Prognosis, Stepped care, General practice, Randomized controlled trial

## Abstract

**Background:**

Depression is a highly prevalent and costly disorder. Effective treatments are available but are not always delivered to the right person at the right time, with both under- and over-treatment a problem. Up to half the patients presenting to general practice report symptoms of depression, but general practitioners have no systematic way of efficiently identifying level of need and allocating treatment accordingly. Therefore, our team developed a new clinical prediction tool (CPT) to assist with this task. The CPT predicts depressive symptom severity in three months’ time and based on these scores classifies individuals into three groups (minimal/mild, moderate, severe), then provides a matched treatment recommendation. This study aims to test whether using the CPT reduces depressive symptoms at three months compared with usual care.

**Methods:**

The Target-D study is an individually randomized controlled trial. Participants will be 1320 general practice patients with depressive symptoms who will be approached in the practice waiting room by a research assistant and invited to complete eligibility screening on an iPad. Eligible patients will provide informed consent and complete the CPT on a purpose-built website. A computer-generated allocation sequence stratified by practice and depressive symptom severity group, will randomly assign participants to intervention (treatment recommendation matched to predicted depressive symptom severity group) or comparison (usual care plus Target-D attention control) arms. Follow-up assessments will be completed online at three and 12 months. The primary outcome is depressive symptom severity at three months. Secondary outcomes include anxiety, mental health self-efficacy, quality of life, and cost-effectiveness. Intention-to-treat analyses will test for differences in outcome means between study arms overall and by depressive symptom severity group.

**Discussion:**

To our knowledge, this is the first depressive symptom stratification tool designed for primary care which takes a prognosis-based approach to provide a tailored treatment recommendation. If shown to be effective, this tool could be used to assist general practitioners to implement stepped mental-healthcare models and contribute to a more efficient and effective mental health system.

**Trial registration:**

Australian New Zealand Clinical Trials Registry (ANZCTR 12616000537459). Retrospectively registered on 27 April 2016. See Additional file 1 for trial registration data.

**Electronic supplementary material:**

The online version of this article (doi:10.1186/s13063-017-2089-y) contains supplementary material, which is available to authorized users.

## Background

### Background and rationale

Depression affects at least 350 million people worldwide [1] and is a leading cause of non-fatal burden of disease [2]. It is costly to individuals in terms of relationships and functioning and to society in terms of direct medical costs and costs due to loss of individual productivity [3]. Despite significant investments in mental health globally, there is no evidence of a reduction in the burden of disease associated with depression [4]. One of the biggest challenges facing mental healthcare systems is the need to develop efficient methods of allocating clinically effective treatment in a cost-effective way to the people that need them most [5].

The majority of depression cases are identified, treated, and followed up in primary care [6]. However, general practitioners (GPs) have been criticized for both under- and over-diagnosing, and treating, depression [7–10]. For example, only 16% of Australians with case level depression or anxiety receive an adequate “dose” of an evidence-based intervention consistent with treatment guidelines [9]. On the other hand, antidepressant prescriptions far outnumber patients for whom such medication is indicated [11].

Multi-country studies report that 24–55% of patients in primary care waiting rooms meet screening criteria for being “probably depressed” [12]. However, among this population of “probably depressed,” a range of illness trajectories exist which contribute to the difficulty experienced by practitioners in making a diagnosis and treatment recommendation [13–18]. It may be that the heterogeneity of clinical presentation which characterizes depression in the primary care setting is leading to the simultaneous problems of both over- and under-diagnosis and treatment.

Currently, there is a mismatch in primary care between patient need and the depression care received, possibly as a result of poor treatment allocation. For example, delivery of intensive interventions to people with minimal or mild symptoms is unnecessarily costly and risks medicalizing normal fluctuations in mood [19]. Conversely, without a targeted intensive intervention, people likely to experience severe and chronic symptoms are likely to experience significant disability, which could have been avoided [20, 21].

Stepped care models, in which patients are, in the first instance, provided with the least time- and resource-intensive intervention that will be effective [22], have been promoted as a potential solution to the problem of poor treatment allocation. Although limited empirical evidence exists as to their effectiveness [23], these models make intuitive sense and feature in both clinical guidelines and policy directives in Australia [24] and the UK [22]. Currently, a key obstacle to the implementation of stepped care models is the lack of effective treatment allocation tools to guide GPs in matching the intensity of treatment to a patient’s needs. In particular, current recommendations focus on matching treatment to the patient’s current symptom severity, rather than patient’s likely course of illness in the future. This is out of step with the management of other conditions (e.g. cardiovascular disease or cancer), which routinely take prognostic factors into account when deciding upon treatment recommendations. Further, it contrasts with calls for research, policy, and practice to make prognosis-based intervention a priority [25]. To date, there has been no quick and systematic way for GPs to identify depression outcomes that a particular person is likely to experience in the future and recommend treatment accordingly.

One option for systematizing treatment recommendations is to use a clinical prediction tool (CPT). CPTs are based on a prognostic model that uses clinical and non-clinical information to estimate an individual’s risk of a specific outcome [26]. The prognostic model is applied in clinical practice using the CPT which stratifies patients into different treatments according to their estimated risk [27]. While CPTs are common in many fields of medicine, they are not readily available for use in mental-healthcare settings. [28]

To address this gap, we wanted to develop a simple, easy-to-use CPT to assist primary care clinicians to triage patients presenting with depressive symptoms and allocate to appropriate treatment. First, we investigated whether an existing prognostic model for depression could be used to build the CPT. We identified several prognostic models that have been developed to predict current [29, 30] or future major depression [31–34] or treatment response [35–37]. However, none of these prognostic models were found to be suitable for incorporating into a CPT which could be easily administered in routine care [38].

Therefore, we developed a novel prognostic model using data from the *diamond* cohort study [39] to predict depressive symptom severity at three months [38]. It comprises 17 items assessing depressive symptom severity at baseline as measured by the Patient Health Questionnaire-9 (PHQ-9) [40]: sex; current anxiety; history of depression; presence of chronic illness affecting daily functioning; self-rated health; living alone; and perceived ability to manage on available income. Based on an individual’s score, he or she is stratified into one of three groups based on predicted depressive symptom scores at three months; namely, minimal/mild (those predicted to have a PHQ score of ≤ 10 at three months), moderate (PHQ > 10 and < 13), and severe (≥13). Cutoffs for the three groups were established during the development of the *diamond* CPT and are explained in full elsewhere [38]. In the intervention being tested in the current study, individuals are then:Presented with feedback reflecting their responses to the CPT;Provided an opportunity to set priorities and reflect on motivation to change; andPresented with an evidence-based treatment recommendation matched to group classification.

The presentation of feedback and treatment recommendation was informed by the principles of motivational interviewing [41] and an iterative development process employing user-centered design principles to ensure the information is presented in a way that is meaningful and engaging for participants [42].

### Objectives

The Target-D randomized controlled trial (RCT) aims to test whether using the *diamond* CPT to tailor treatment recommendations to an individual’s predicted depressive symptom severity is a clinically effective and economically efficient way of reducing depressive symptoms, relative to usual care. This paper presents the study protocol for the Target-D RCT, adhering to the SPIRIT guidelines for intervention trial designs ([43]; see Additional file 2 for SPIRIT checklist).

The primary objective of the Target-D trial is to determine if using the *diamond* CPT to triage individuals with depressive symptoms into symptom severity-appropriate treatment reduces depressive symptoms at three months compared with usual care.

Secondary objectives are to: (1) test whether individuals in the intervention and comparison arms differ in depressive symptom severity at 12 months, quality of life, anxiety symptoms, self-efficacy, and health service use at three and 12 months; (2) determine whether the outcomes differ between the two study arms within each of the three depressive symptom severity groups; and (3) evaluate the cost-effectiveness of the new model of care compared to usual care.

### Trial design

Target-D is a stratified individually RCT with two parallel arms, modelled on the trial undertaken by Hill et al. who tested the stratified management of low back pain [44]. Participants will be randomized to the intervention or usual care arm with 1:1 allocation, stratified by general practice and predicted depressive symptom severity group. Participants in the intervention arm will be categorized into one of three treatment groups according to their *diamond* CPT results; participants in the usual care arm will complete the *diamond* CPT but will not receive feedback, an opportunity for reflection, or a treatment recommendation specific to their predicted depressive symptom severity. An intention-to-treat (ITT) approach will be used in the analysis (explained further below).

## Methods

### Participants, interventions, and outcomes

#### Study setting

The study will be conducted in at least ten general practices in Victoria, Australia (see Additional file 3 for the location of study sites).

### Eligibility criteria

General practices will be eligible if they: see more than 50 adults aged 18–65 years per day; agree to waiting room screening; have a private space available to be used for the Target-D intervention; and have the majority of their GPs willing collaborate with the Target-D team.

Patients attending participating general practices will be assessed for eligibility using a self-report survey delivered via an iPad. Patients will be eligible if they score 2 or more on the two-item version of the Patient Health Questionnaire (PHQ-2) [45] (indicating depressive symptoms but not necessarily a diagnosis of major depressive disorder), are aged 18–65 years, have access to the Internet for the duration of follow-up, have sufficient written English to follow an Internet-based cognitive behavioral therapy (iCBT) program, have not changed depression medication in the past month (if they take such medication), and agree to randomization to either the usual care or intervention arm. They will be ineligible if they are currently taking antipsychotic medication, are regularly seeing or planning to see a psychologist in the next three months, or are currently using an iCBT program. Eligible patients will be asked to provide informed consent online (see Additional file 4) and complete baseline measures prior to completing the *diamond* CPT.

### Intervention

Participants will complete the *diamond* CPT online on a purpose-built study website (henceforth referred to as the Target-D website). They will then be contacted by phone by a trained research assistant (RA) to provide encouragement and support and answer questions as necessary. This phone call will occur within one week of *diamond* CPT completion.

#### Intervention arm

As described above, the intervention being tested comprises feedback on CPT responses, an opportunity to set priorities, and a treatment recommendation (based on predicted depressive symptom severity). Immediately after completing the *diamond* CPT, participants in the intervention arm will see these components displayed on sequential pages of the Target-D website.

The follow-up phone call from an RA will involve a discussion about the treatment recommendation they received, using the results of the *diamond* CPT to tailor the discussion to the individual’s classification. To encourage treatment engagement, this discussion will use motivational interviewing, an approach to conversations that promotes collaboration and aims to strengthen the person’s motivation and commitment to making a change [41].

The recommended treatment for each of the three groups were selected based on a stepped care approach [22], with treatment intensity lowest in the minimal/mild group and highest in the severe group. To select the specific treatments offered to each level of intensity, we examined existing primary care data from the *diamond* cohort study to describe the characteristics, treatment, and service use of individuals stratified to each group. We also reviewed systematic reviews of the evidence relevant to each group and presented these findings to our investigator team to inform treatments offered. Another comprehensive description of the interventions delivered, using the TIDier checklist, will be included in the primary outcome paper as per Hoffmann et al. [46] and CONSORT guidelines.

##### Minimal/mild depressive symptoms at three months

Participants who are likely to have minimal or mild depressive symptoms at three months will be offered self-help and automated follow-up using the myCompass iCBT program which has been shown in randomized trials to be effective in improving outcomes for patients with mild depression [47, 48]. myCompass is an interactive, self-help Internet resource consisting of information, accounts of others’ experiences, treatment modules with home tasks, and mood tracking functions. myCompass uses an internal algorithm to recommend components tailored to participant symptoms and needs. Participants can choose to follow the recommendation or not and may undertake components of the program in any order.

Participants in the minimal/mild group will receive two automated emails from the research team to encourage uptake and adherence to the treatment recommendation. These emails will be sent immediately after the participant receives the recommendation to use myCompass and one week later and are in addition to any correspondence the participant receives from the myCompass program.^1^ Emails will provide participants with the link to myCompass, encouragement to get started, and reminders of some of the benefits of the program. This will mimic what would be feasible in the routine clinical setting.

##### Moderate depressive symptoms at three months

The moderate group will be offered clinician-guided iCBT via the *Worry and Sadness* course in the This Way Up program, which has randomized trial evidence of effectiveness in reducing moderate symptoms of depression [49]. This Way Up comprises six structured online lessons using CBT principles and includes lessons in the form of an illustrated story about someone with depression, printable summaries, and homework assignments, and symptom monitoring at the beginning of each session [49]. Lessons are completed in a linear order and each becomes available five days after the previous lesson is completed.

Target-D will follow standard This Way Up protocol, with participants provided with weekly individualized support via phone/email, until they have completed Lesson Two [49]. Support will include positive encouragement to commence or continue treatment, reiterate the importance of homework completion, and respond to general questions by referring back to program materials. This role will be filled by RAs, in line with evidence supporting the effectiveness of non-clinician provided support to This Way Up users [50]. In keeping with published protocol [49], after the completion of Lesson Two phone contact will be made in response to patient request or a deterioration in condition (defined as an increase of ≥ 5 on the PHQ-9 [51]).

##### Severe depressive symptoms at three months

The severe group will be offered collaborative care, an enhanced form of patient care shown to be effective for treatment of moderate to severe depression in primary care [21, 52–54]. Collaborative care is defined as including four key ingredients: a multi-professional approach to patient care; a structured management plan; scheduled follow-ups; and coordinated communication between health professionals involved in management [21, 55]. Target-D participants involved in collaborative care will receive eight appointments with a trained case manager (CM). The CM role will be filled by a non-mental-health specialist such as a registered nurse. This decision was made as it is in keeping with the role filled by practice nurses in managing other chronic conditions such as diabetes and thus should enhance scalability of the Target-D model of care should it be effective.

The Target-D approach to collaborative care is underpinned by the principles of motivational interviewing, to enhance patient engagement and action. The Target-D CM will receive training in the intervention approach by a qualified psychologist and will receive regular supervision and support from the psychologist and project manager (SF) throughout the trial.

Patients in this group will be reminded of upcoming appointments with the Target-D CM via SMS. After each appointment, patients will receive an email from their CM summarizing their discussion and outlining the actions the patient intends to take to manage his/her mental health. With the patient’s consent, the CM will also send a copy of this email to the treating GP and other professionals involved in the patient’s mental healthcare.

#### Comparison arm

Participants randomized to the comparison arm will access health services as usual. The choice of “usual care” as a comparator was made as the study aims to determine the extent to which the intervention improves (or worsens) patient outcomes relative to standard practice [56]. Participants in this arm will also receive some non-therapeutic attention from Target-D to control for any effect of contact with the study team following completion of the *diamond* CPT; thus, this study arm is referred to as “Usual care plus Target-D” or UC+. UC+ participants will be blinded to their depressive symptom severity group allocation and will not receive a tailored treatment recommendation. Instead, they will see a screen on the Target-D website advising them that they will be asked to provide feedback on: (1) their opinions on research in primary care; and (2) how they normally manage their emotional health and wellbeing. Similar to the procedure for intervention participants, those in the usual care arm will be contacted by phone by an RA within one week of *diamond* CPT completion. The RA will reiterate the importance of the participant’s involvement in the study, ask a series of structured questions about the participant’s views on research and the involvement of their general practice in research, and advise the participant that he or she will be contacted via email in 12 weeks.

#### Modifications

The nature of the study interventions is such that no substantive modifications are anticipated. Patients in the minimal/mild and moderate groups may discontinue using the online program at any time and treatment for those in the severe group may be discontinued at patient request.

If any participant indicates high levels of suicidal ideation during contact with a member of the study team (as indicated by a response of “nearly every day” to question 9 on the PHQ-9: “thoughts that you would be better off dead or of hurting yourself in some way”), regardless of study arm allocation, a standardized suicidal ideation assessment used previously by the study team will be administered and the patient’s GP alerted. This will be reported as an adverse event but is unlikely to result in treatment discontinuation or modification. The assessment will determine if the adverse event was related directly to the intervention or other circumstances not intervention related.

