#### Blinding

Due to the nature of the intervention, participants cannot be blinded to their treatment allocation. However, GPs will not be notified of their patients’ allocation to either intervention or comparison arm. No emergency unblinding of GPs is anticipated, including in the case of the research team alerting the GP to patient suicidality. As outcome assessment is conducted online, no blinding of outcome assessors is required. All study analyses will be conducted by a statistician blind to participants’ allocation; study arm allocation will be coded as A or B, with the code for the study arm revealed only after data are analyzed.

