### Data collection

Participant data will be collected from intervention and comparison arms using validated questionnaires on the Target-D website at screening, baseline and three and 12 months (Fig. 2). *diamond* CPT data will also be collected on the Target-D website. Participants will receive an automated email from the website at 80 and 358 days after *diamond* CPT completion with a unique link to the three-month and 12-month survey, respectively. Participants will be informed that if they decide to withdraw from the study, the data already provided will be retained and used in the analyses unless they request otherwise.

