#### Primary outcome

Depressive symptom severity will be assessed at each timepoint using the PHQ-9. The PHQ-9 assesses the nine DSM symptoms of depression over the last two weeks using a 4-point Likert scale (where 0 = “not at all” and 3 = “nearly every day”). Total scores are in the range of 0–27, with suggested cut points of 5, 10, and 15 indicating mild, moderate, and severe depression, respectively [40]. The PHQ-9 is a validated diagnostic measure in primary care [65], with demonstrated efficacy and sensitivity as an outcome measure for treatment trials with a recommended Reliable Change Index [51].

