### Retention

To encourage retention at each study time point, non-responders will receive up to five reminders in total via phone, text, and email. These reminders will also provide the option of completing the baseline, three-month, or 12-month survey over the phone with an RA or being mailed a hard copy of the questionnaire to complete and return via reply paid envelope. At three and 12 months, participants who still do not complete the survey will be offered the option of completing the primary outcome measure (PHQ-9) alone. Outcome assessments may be completed in multiple sittings, with participants provided the option of saving their responses and returning later via a link emailed to them upon exiting the survey.

To acknowledge the time spent by participants and to further promote retention at three and 12 months, random draws for a $100 gift card will be conducted monthly for each follow-up survey, with all participants who completed the survey in the previous month eligible to receive a gift card. The selected participant will be contacted via phone and email. Participants will be advised of the draw in the initial email with their unique link to the relevant survey and in subsequent reminders.

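### The both-arm suicide-risk rule is tied to staff contact, but its only named indicator, PHQ-9 item 9, is normally answered online with no staff involved

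*Protocol article*

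**What the plan says.** Under Modifications, the rule begins "If any participant indicates high levels of suicidal ideation during contact with a member of the study team". A parenthesis then defines high ideation as the most frequent response option on PHQ-9 question 9, and the rule applies whatever the participant's arm. Three things follow: a standardized suicidal ideation assessment, an alert to the GP, and an adverse-event report.

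The article describes collection of the same instrument elsewhere:

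- Measures, Primary outcome: "Depressive symptom severity will be assessed at each timepoint using the PHQ-9".
- Data collection: data in both arms are gathered "using validated questionnaires on the Target-D website at screening, baseline and three and 12 months". For follow-up, "Participants will receive an automated email from the website at 80 and 358 days after" completion of the prediction tool, with a unique survey link.
- Data management: participants key their own answers into the website, and the coded data are downloaded weekly.
- Blinding: "As outcome assessment is conducted online, no blinding of outcome assessors is required".
- Retention, for non-responders: "These reminders will also provide the option of completing the baseline, three-month, or 12-month survey over the phone with an RA", or alternatively "being mailed a hard copy of the questionnaire to complete and return via reply paid envelope".

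**The concern.** The rule has a scope (ideation shown while in contact with the team) and a measure (one questionnaire item). The measure is ordinarily collected outside that scope. A participant who answers the online survey promptly and reports such thoughts nearly every day is not, on the printed words, covered. One who ignores the link and later gives the identical answer by phone to a research assistant is covered. The route of completion, which has nothing to do with clinical risk, would decide whether the assessment, the GP alert and the adverse-event record follow.

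What is at stake is individual safety. This is the only individual suicide-risk rule covering both arms that the article prints, and the trial recruits people because they have depressive symptoms.

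**Working it through.** The article gives no figure to reproduce, so the check is textual: take each route by which item 9 can be answered and ask whether the printed condition is met.

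| Route | Where described | Staff contact when item 9 is answered? | Inside the printed condition? |
|---|---|---|---|
| Website, three and 12 months (default) | Data collection; Data management; Blinding | No: automated email, self-entry, no assessor | No |
| Website, baseline | Data collection; Allocation | Not stated; a research assistant recruits in the waiting room and may be nearby, but the entry is the participant's own | Unclear |
| Mailed form (fallback) | Retention | No | No |
| Phone with a research assistant (fallback) | Retention | Yes | Yes |

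The only documented route that clearly meets the condition is therefore the phone fallback.

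Next, does any other section widen the trigger?

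- **Blinding** refers to unblinding, "including in the case of the research team alerting the GP to patient suicidality". This confirms that alerts happen but does not say which answers start them.
- **Monitoring** says adverse events are assessed through routine data collection. That concerns recording; it does not extend the ideation assessment or the GP alert to online answers.
- **Ethics and dissemination** allows confidentiality to be broken where someone is in danger. It permits action but sets no trigger.
- **Moderate depressive symptoms at three months** has a deterioration rule, a PHQ-9 rise of 5 or more. It uses the total score and serves one intervention group only.
- **Comparison arm** describes the scheduled usual-care call as questions about research and the practice's part in it. The PHQ-9 is not mentioned.

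None of these brings an online or paper answer within the rule.

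A count of affected answers would need the share of surveys completed by phone and the frequency of the top response on item 9. The article gives neither, so no count is offered.

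**The case against.** The strongest reply is that the text supplies its own remedy. The parenthesis equates high ideation with an item 9 answer, for any participant in either arm. A reading that shuts out the website leaves the rule nearly empty, so it is probably not what was meant. The article also uses the idea of contact loosely: the Comparison arm section speaks of participants being contacted by email at 12 weeks. The reference to GP alerts under Blinding fits the broad reading. In addition, the rule relies on an existing assessment procedure that is not reproduced, and website flags are the kind of operational detail an article leaves to a fuller document.

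Much of this stands. It makes loose phrasing more likely than a deliberate exclusion, and it means the absence of a described website alert is not itself a fault. It does not remove the point. The article did not leave the trigger to another document: it printed the threshold, the arms, the response and the reporting status, and added a limiting condition that does not fit how the measure is collected. Someone following those words would leave out the default route.

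Two stronger readings are tempting and should not be drawn:

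- **More recorded events in the intervention arm.** A reader might infer this from its greater staff contact, for example eight case-manager appointments in the severe group, and go on to suppose that safety data sent to the data monitoring committee are distorted. The article does not say item 9 is asked at the research-assistant call, in the guided online support or at those appointments. The one documented staff-administered route, phone completion, is open to both arms. Monitoring describes reporting events to the committee but no between-arm comparison of event rates.
- **Online answers will in fact go unattended.** The article does not show this. The team may already follow them up.

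**Conclusion.** The point holds as a mismatch between a printed safety condition and its printed measure. Taken literally, the rule covers a top-category item 9 answer given by phone and omits the same answer given on the website at follow-up or on paper; baseline is unclear. This rests only on the words of the article and on reading contact as live contact with a team member. If the authors meant any response, or an operational alert exists elsewhere, the practical effect is nil and only the wording is wrong. The number of participants affected is unknown. The primary estimand, sample size and analysis do not depend on it. It is a cheap improvement for patient safety, of minor severity.

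**What to change.** Reword the trigger under Modifications so that it is met by a response of nearly every day to PHQ-9 item 9, by any collection route (website, paper or phone), in either arm. State that online answers are flagged to an existing study role. Keep the threshold, the ideation assessment, the GP alert and the adverse-event report as they are.

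The cost is one change of wording, a website notification if none exists, and possibly an ethics submission. The downside is possibly more ideation assessments and GP alerts for the existing team. An alert raised by the three-month survey cannot alter the three-month PHQ-9, which is already recorded. Alerts raised by baseline answers rest on data collected before randomization, so who triggers one cannot depend on the arm assigned. If online answers are already followed up, only the wording changes.
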